### Statistical analyses

2.11

Data will be cleaned, analyzed, and visualized in MATLAB_R2023b software. The missing data will be reported and deleted by case. The data will be reported as mean and standard deviation. The significance level will be set at p < 0.05. Linear mixed-effect model (LMM) with fixed-effect factors for time, condition, and their interaction, and a random intercept for ID, will be applied to each performance variable (i.e., RT, RAcc, LT, LAcc) and subjective fatigue variable (i.e., MVAS, RPE). The Shapiro–Wilk test will be conducted to assess the normality of the residuals. Sphericity will be evaluated using Mauchly's test. When appropriate, Bonferroni post-hoc tests will be used. Other subjective perceptions (i.e., VAS-Re, VAS-Enj, NASA-TLX) and HRmean will be compared between conditions via paired sample t-tests. The normality of the difference scores will be verified using the Shapiro–Wilk test. If violated, the non-parametric Wilcoxon signed-rank test will be used instead. For significant effects in LMM, partial eta-squared will be calculated. For t-tests, Cohen's d will be computed. The classification criteria will follow Cohen's convention: for partial eta-squared, 0.01 = small, 0.06 = medium, and 0.14 = large effect; for d, 0.2 = small, 0.5 = medium, 0.8 = large effect.

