### Participants

2.3

To address the primary purpose, the sample size has been calculated via G∗Power 3.1 based on the intended time and condition interaction effect. In a previous study, Harris et al. (2020) used a similar design to compare the training effect in a VR environment with the real-world environment on motor skill performance [24]. They reported a significant, partial eta squared = 0.12 interaction effect. Extracting the effect size value, which corresponds to a Cohen's f = 0.369, with α = 0.05, power (1−β) = 0.90, correlation among repeated measures = 0.5, and non-sphericity correction ε = 1, the minimum required sample size has been determined to be 15. Due to the practical constraints in athletes' recruitment, combined with the possible dropouts (>15%) and the counterbalanced consideration for matched pairs, 20 participants will be recruited to address the first hypothesis.

Active, senior Epee fencers from a university fencing club, featuring a Tier 2–3 (i.e., a trained to well-trained) profile [25], will be considered and screened for eligibility. Eligible participants will receive an email/paper file with an official invitation and informed consent. However, the actual purposes will be masked (i.e., single-blind) by the experience of new VR devices and the internal performance tests in scheduled training sessions. Unblinding procedures will be conducted after completion of data analysis. Following completion of informed consent, online questionnaires will be sent to collect demographic, health, fencing, and lifestyle information. The information will be recorded for further eligibility screening (detailed criteria are seen in Table 1). Participants retain the right to stop participation in the study at any moment.

**Table 1 tbl1:** The detailed inclusion and exclusion criteria for eligibility.

	Inclusion criteria	Exclusion criteria
1	Aged 18–35 years	Concurrently taking the role of assistant coach/trainer
2	Active Epee fencers from the university club	Training as a Sabre or Foil fencer
3	Being enrolled as a university student	High myopia (no glasses) and red/green color vision defects
4	Understanding concepts both in Chinese and English	Having sleep disorders
5	Being able to provide informed consent individually	Taking any medical treatment during the study
6	Training ∼3 times per week for a competitive purpose	Taking any academic course/examination before tests

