### Procedures

2.4

Eligible fencers visit the club pistes 3 times at a fixed slot (e.g., weekly routine training session at 15:00–17:30 to improve adherence), including a familiarization and two conditions (EXP/CON). The washout period will be at least 48h between conditions. The EXP and CON will take approximately 50min. Upon arrival and after preparation, a 15-min standardized general warm-up will be organized by the physical coach before T0. Next, 10min technical drills will be provided by the head coach. In EXP, the two fencers will start VC on their own for 10min. In CON, the paired fencers will conduct TC in the same format for 10min. Immediately before and after the 20-min specialized warm-up (i.e., technical drills and VC/TC), standardized measurements at T0 and T2 will be performed as follows: a 1-min digital questionnaire to collect subjective perceptions, a brief psychomotor vigilance test (PVT-B) to evaluate the reaction performance for 3min, and an Epee fencing-specific test (FST) to assess the reaction speed and lunge attack accuracy of the random targets for another 3min. Between the technical drills and VC/TC (T1), the questionnaire will be prompted to the fencers. Participants will be equipped with HR chest bands (Firstbeat, Garmin, Finland) throughout conditions to check the physiological response to VC/TC.

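### Read as participant-level deletion, the missing-data rule discards records that the planned mixed model can use; the dropout allowance also does not mention partner loss.

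*Protocol article*

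**What the plan says.** Section 2.11 (Statistical analyses) gives one rule for missing data: "The missing data will be reported and deleted by case". It does not say whether a case is a fencer or a single row of data.

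The same paragraph specifies, for each performance and subjective fatigue variable, a "Linear mixed-effect model (LMM) with fixed-effect factors for time, condition, and their interaction, and a random intercept for ID". It adds Mauchly's test, and paired tests for the remaining questionnaire items and mean heart rate.

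Section 2.3 (Participants) derives a minimum of 15 and then reaches the recruitment target: "combined with the possible dropouts (>15%) and the counterbalanced consideration for matched pairs, 20 participants will be recruited". Pairs appear there only in connection with counterbalancing.

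Section 2.1 makes the matched pair the unit of random assignment. Section 2.4 (Procedures) has virtual combat done individually, but for the control condition: "In CON, the paired fencers will conduct TC in the same format for 10min". The article does not say what happens if one partner is absent.

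**The concern.** The deletion rule and the chosen model do not fit together. A likelihood-based mixed model estimates time, condition and their interaction from whatever records a fencer has, and is valid if data are missing at random given what was observed. Removing every fencer with a gap discards observed data. It also requires, in effect, that complete fencers be representative of all fencers, which is a stronger condition. With 20 fencers, each one removed matters.

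The participant reading is the more natural one. Casewise deletion ordinarily means removing the subject, and Mauchly's test in the same paragraph needs each fencer's full set of measurements.

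A second issue comes from the design. Traditional combat is fought within the pair, so a fencer who leaves before the control visit can leave the partner without an opponent. Under participant-level deletion, that partner's complete virtual-combat data would then also be dropped.

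**Working it through.** **1. Cost of participant-level deletion**

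Inputs: 20 fencers (section 2.3). Each performance variable has four records per fencer (T0 and T2 in two conditions). Mental fatigue and perceived exertion have six if T1 is modelled (section 2.9.1). Assumption, not in the article: each record is missing independently with probability 5%.

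- Complete on four records: 20 × 0.95⁴ = 20 × 0.8145 = 16.3 fencers.
- Complete on six records: 20 × 0.95⁶ = 20 × 0.7351 = 14.7 fencers.
- Four records: 80 × 0.95 = 76 records are observed. Complete fencers supply 16.3 × 4 = 65.2, so about 10.8 observed records are discarded.
- Six records: 120 × 0.95 = 114 are observed, 14.7 × 6 = 88.2 are kept, and about 25.8 are discarded.

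A model fitted to all available records discards none of these.

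**2. The article's sample size**

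Inputs (section 2.3): partial eta squared 0.12, "which corresponds to a Cohen's f = 0.369" (√(0.12/0.88) = 0.369), α = 0.05, "power (1−β) = 0.90", "correlation among repeated measures = 0.5" and "non-sphericity correction ε = 1". The number of measurements m is not stated.

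Repeated-measures F test, one group: λ = f²·N·m/(1 − ρ), df₁ = m − 1, df₂ = (N − 1)(m − 1).

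- m = 2 gives N = 22, m = 3 gives 18, and m = 4 gives 15. So m = 4 reproduces the stated figure and is assumed below.
- At N = 15: λ = 0.1364 × 15 × 4/0.5 = 16.4, df 3 and 42, power 0.915.
- At other sizes: 0.934 at 16, 0.892 at 14, 0.827 at 12.

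This set-up is used only to gauge losses on the article's own scale.

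**3. Dropout allowance**

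Counted as individuals, 15/0.85 = 17.6, so 18. Going to 20 is consistent with rounding up for pairs and orders. The article does not state the unit of its dropout figure.

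Assumptions for pair dependence: independent dropout with probability d, five pairs per order, no substitute or re-pairing, and an unpartnered fencer counted as incomplete.

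- All loss before the control visit: a pair survives with probability (1 − d)². At d = 0.15, 0.85² = 0.7225 and 20 × 0.7225 = 14.45 expected completers. At least 15 completers means at least 8 of 10 intact pairs; the binomial probability is 0.44.
- All loss between visits: only pairs starting with virtual combat lose the partner's control data. 10 × 0.7225 + 10 × 0.85 = 7.2 + 8.5 = 15.7 expected; the probability of at least 15 is 0.71 (simulation).
- Individuals: 20 × 0.85 = 17 expected; the probability of at least 15 is 0.93.

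| Dropout | Individuals: expected, P(≥15) | Loss between visits | Loss before control visit |
|---|---|---|---|
| 10% | 18.0, 0.99 | 17.1, 0.89 | 16.2, 0.71 |
| 15% | 17.0, 0.93 | 15.7, 0.71 | 14.45, 0.44 |
| 20% | 16.0, 0.80 | 14.4, 0.50 | 12.8, 0.24 |

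**The case against.** **A case may be a row.** If so, the rule describes what the mixed model does anyway, and little is lost. This stands as a possible reading, which is why the main point is conditional. The sentence still needs changing, because the two readings produce different analysis datasets. For the paired tests, leaving out a fencer without both conditions is unavoidable and is not criticised here.

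**The 5% rate has no source in the article.** That is correct; it only illustrates scale. Several features limit missingness: the tablet scales require confirmation before submission, and reaction and lunge times are averaged over valid trials. Models are fitted per variable, so a reader should not infer that one missing slider response removes a fencer's fencing-test data. The figure of 14.7 applies only if T1 is modelled, and section 2.1 presents T1 as a standardisation check. On T0 and T2 alone the figure is 16.3, still above 15.

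**Partner loss is a worst case.** A reader might infer that 20 recruits fail to secure 15 completers. The article does not support this as a flat statement. The 0.44 needs every loss to fall before the control visit, with no stand-in and no re-pairing. Loss wholly between visits gives 0.71. Two dropouts leave at least 16 completers in either scenario. A condensed article may leave substitution arrangements to the full protocol. What stands is that section 2.3 does not mention partner loss.

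**Deletion breaks the counterbalancing.** A reader might also infer this from the unequal losses (7.2 against 8.5 expected completers by order). The imbalance comes from the dropout itself, and using all available records does not restore it.

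**Conclusion.** The point holds in a conditional form. The stated rule, on its ordinary reading, removes fencers whose remaining records the planned model could use. It loses precision and relies on a stronger assumption than missing at random, for no gain. At an assumed 5% of records missing, 16.3 of 20 fencers would remain on four records, or 14.7 on six.

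The dropout point is secondary. It rests on independent dropout and no substitute partner, neither of which the article settles. Under those assumptions, 15% dropout gives 14.5 to 15.7 expected completers instead of 17. On the article's own method with four measurements assumed, 14 completers give power 0.892 against a target of 0.90. The loss becomes material at around 12 (0.827). This supports stating the dependence openly, but not a claim that the study is undersized on this account or that more fencers must be enrolled.

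**What to change.** In section 2.11, replace the missing-data sentence with, for example: *The linear mixed models use all available records (REML, assuming missing at random), with no deletion of fencers who have some missing records. A complete-case analysis is reported as a sensitivity analysis. Paired tests use fencers with both conditions.* Add that the available data of a fencer whose partner leaves are kept.

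In section 2.3, add one sentence saying that the control condition needs both partners and that the dropout allowance is therefore conditional on how many pairs are broken, giving the expected range of completers. Recruitment can stay at 20. Report completers by order, since the revised analysis does not itself rebalance the sequences.

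The cost is a few sentences of text and one extra model run per variable, with no added data collection or enrolment.

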Importantly, VR is reported to consistently stimulate the autonomic nervous system, as evidenced by increases in heart rate (HR) and skin resistance [19]. It can also lead to reduced vagal activity in the parasympathetic system, as shown by lower HR variability [20], indicating a similar mental fatigue state [21]. Research further suggests that engaging with immersive virtual content increases cognitive demand, potentially causing cognitive decline due to the user's limited attentional resource [22]. Despite being a promising technology that engages the specific motor-cognitive processes that are critical for fencing warm-up and competition-related performance, key concerns remain. It is not yet explored to what extent on-field VR combat can prime the real-world performance, nor what the potential effects are on mental fatigue in fencers. Consequently, this study will compare the effects of virtual combat (using VR) with those of traditional warm-up combat in the specialized warm-up section, on fencing-specific performance and fencers' fatigue levels. This study seeks to inform practitioners to evaluate and optimise warm-up practices. It is particularly relevant when access to an appropriate competitive sparring partner may be limited by availability, or an adapted preparation is required in official competitions, in consideration of the fencer's initial fatigue state.

*Aims*. The primary aim is to compare the acute effects of a 10-min VR combat with a 10-min traditional one-on-one combat during the 20-min specialized warm-up section, on subsequent fencing-specific psychomotor performance and subjective mental and physical fatigue levels in fencers. The secondary aims are: (1) to explore the athlete's psychological experience of the task load, readiness, and enjoyment; (2) to explore the behavioral indicators of mental fatigue and physiological response in the two specialized warm-up conditions.

*Hypotheses*. The hypotheses are: (1) VR combat will benefit the fencing-specific psychomotor performance, while inducing less subjective physical and mental fatigue due to the entertaining game nature. (2) Fencers will perceive less task load in a similar HR response, but more readiness and enjoyment after the embedded VR combat than traditional one-on-one combat. (3) The behavioral indicators of mental fatigue will align with the subjective perceptions of fencers.

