#### Epee fencing-specific test

2.9.3

The study follows the test settings and instructions from Varesco et al. [4]. The FST consists of three shuttles (forward and backward) over 2m for men and 1.75m for women Epee fencers. This adjustment for the women's group has been deemed necessary based on the height difference. Shuttles must be completed within 9s. Participants will be taught to focus their attention on the eight flash-impact sensors (ReactionX Pro, China) attached to a fencer-shaped dummy (2 × 1m), as presented in Fig. 4. After the 9s shuttling, a green-colored sensor will be shown as the random lunge attack target. The target will undergo a randomization with replacement, that is, the same one could be presented multiple times. Once the target is presented, participants will be instructed to execute a lunge to deliver a valid hit on the middle of the sensor (i.e., a final attack to score) via the sword tip as quickly as possible. Furthermore, to better simulate the possible correction and reaction inhibition in real fencing, an incongruent cue will be presented in 10% of the trials [4]: a sensor will be flashed in red color for 300 ms before the real green target is shown. The incongruent cue will be presented close to the real target (i.e., within 40 cm) to mimic the real-world fast displacement in fencing. The trial will be separated by 9s for passive rest to simulate the temporal demands (i.e., work-to-rest ratio of 1:1) in Epee. Thus, each trial will last 18s. One FST will include 10 trials for 3min. The test outcomes will be the number of lunges hits on the real targets, hits on the wrong target, misses the targets, and the time from the moment each target is activated (i.e., lights up) to the moment it is hit or missed. Then, the average value of the lunge reaction time (LT) of the valid hits and the lunge attack accuracy (LAcc) will be calculated for analysis.

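### Four unranked primary-aim outcomes are each tested at 0.05 with no control across them, and partial eta-squared is calculated only for mixed-model effects that reach significance

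*Protocol article*

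**What the plan says.** The primary aim (Introduction, Aims) is to compare the two forms of combat "on subsequent fencing-specific psychomotor performance and subjective mental and physical fatigue levels in fencers". Three constructs are listed and none is put first. The performance construct is the fencing-specific test, from which "the average value of the lunge reaction time (LT) of the valid hits and the lunge attack accuracy (LAcc) will be calculated for analysis" (section 2.9.3). The fatigue constructs are MVAS and RPE (section 2.9.1).

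Section 2.11 says that the linear mixed model "will be applied to each performance variable (i.e., RT, RAcc, LT, LAcc) and subjective fatigue variable (i.e., MVAS, RPE"). The threshold is general: "The significance level will be set at p < 0.05". The only multiplicity step is "When appropriate, Bonferroni post-hoc tests will be used".

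Effect sizes follow two different rules in the same section. For the mixed models: "For significant effects in LMM, partial eta-squared will be calculated". For the paired tests: "For t-tests, Cohen's d will be computed", with no condition attached. Data are also to be summarised as mean and standard deviation, again without condition.

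RT and RAcc, from the vigilance test, have a mixed model too, but they belong to the second secondary aim, "to explore the behavioral indicators of mental fatigue and physiological response in the two specialized warm-up conditions". The sample size (section 2.3) is tied to the time-by-condition interaction and to the first hypothesis. It names no outcome.

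**The concern.** There are two separate problems.

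The first is that the plan does not say which result decides the first hypothesis. Four models are fitted, each has its own 5% chance of a false-positive interaction, and no rule says whether one, some or all must be significant. Post-hoc Bonferroni corrects comparisons within a model after an effect has been found. It does nothing across LT, LAcc, MVAS and RPE. A reader of the results could not tell a planned success from one favourable result out of four.

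The second is that whether a standardised effect size exists for a mixed-model effect depends on its p-value. The mixed models carry every primary-aim outcome, so the filter falls on the results that matter most, while the secondary paired comparisons escape it. Effect sizes selected in this way are too large on average. That matters here because section 2.3 shows how such figures are used: this trial was itself sized from one published significant partial eta-squared.

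**Working it through.** **Inputs.** Alpha 0.05 per test, the list of modelled outcomes and the effect-size rules come from section 2.11. Planned n = 20, minimum n = 15, partial eta-squared 0.12, power 0.90, correlation 0.5 and epsilon 1 come from section 2.3. The correlations between outcomes and the error df below are assumptions, because the article gives neither.

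**The plan's own figure.** f = √(0.12/0.88) = 0.369, as stated. With noncentrality λ = f²·N·m/(1 − ρ), df1 = m − 1 and df2 = (N − 1)(m − 1), m = 4 measurements at N = 15 give λ = 16.4 and power 0.915, so the stated minimum of 15 is reproduced. It uses alpha 0.05 once, with no allowance for four outcomes.

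**Error across outcomes.** Suppose that all four null hypotheses are true and that any one significant interaction counts as support.

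- Two-sided, independent outcomes: 1 − 0.95⁴ = 0.185.
- In the direction favouring VR only, independent outcomes: 1 − 0.975⁴ = 0.096.
- Two-sided, equally correlated outcomes, simulated with n = 20 and 1-df tests: about 17 to 18% at correlation 0.3, 16% at 0.5 and 13% at 0.7.

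**Smallest effect that receives a partial eta-squared.** For a 1-df interaction this is Fcrit/(Fcrit + df2). With 20 fencers, 2 conditions and 2 times there are 80 observations. Removing 1 for the mean, 19 for fencers and 3 for fixed effects leaves 57 error df. If the interaction is instead judged against between-fencer variation in the difference of differences, there are 19.

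| Error df | Fcrit | Smallest significant partial eta-squared |
|---|---|---|
| 19 | 4.38 | 4.38/(4.38 + 19) = 0.187 |
| 57 | 4.01 | 4.01/(4.01 + 57) = 0.066 |

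**Average among those calculated.** Draw F from a noncentral F with λ = [η²/(1 − η²)]·df2, convert to F/(F + df2), and average over draws above Fcrit.

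| True partial eta-squared | Error df | Chance of significance | Mean when significant |
|---|---|---|---|
| 0.06 | 19 | 0.18 | 0.28 |
| 0.06 | 57 | 0.47 | 0.12 |
| 0.12 | 19 | 0.33 | 0.30 |
| 0.12 | 57 | 0.78 | 0.16 |

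At the planning value of 0.12 the calculated effect sizes would average 0.16/0.12 = 1.3 to 0.30/0.12 = 2.5 times the truth. Part of this is the ordinary upward bias of partial eta-squared: with no filter the means are 0.13 (57 df) and 0.15 (19 df). The filter adds the rest.

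**The case against.** **An omission, not an error.** The article is condensed, cites a registration and may have an analysis plan behind it. That would answer a complaint about missing detail. It does not answer this one, because section 2.11 itself fixes the threshold, the list of tested variables, the place of Bonferroni and the significance condition on partial eta-squared.

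**The first hypothesis reads as a conjunction.** It predicts better performance together with less mental and physical fatigue. If every component had to succeed, the error rate would not inflate at all. This stands as a limit on the first part. But no such rule is written, so the inflation is conditional rather than built in.

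**Not all effect sizes are filtered.** A reader might infer that the plan hides every non-significant result. It does not: Cohen's d is computed for all paired tests, and means and SDs are reported throughout. For the same reason an inflation figure for raw mean differences would be beside the point, since the plan does not filter them.

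**Small effects could still be reported.** A reader might infer that an effect in the small range (below 0.06) could never receive a partial eta-squared. That is too broad. If T1 enters the MVAS and RPE models, pooled error df is about 95, and a 1-df effect is significant from 3.94/(3.94 + 95) = 0.040.

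**Six outcomes rather than four.** Counting RT and RAcc would give 1 − 0.95⁶ = 26.5%. The Aims place those two under a secondary, exploratory aim, so that figure overstates the error attached to the primary aim.

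**Conclusion.** The point holds in two limited parts.

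First, four primary-aim outcomes are tested at 0.05 each, with no ranking, no success rule and no control across them. The two-sided family-wise error is at most 18.5%, and about 13 to 18% at assumed correlations of 0.7 to 0.3. About half of it (9.6% if independent) lies in the direction favouring VR. This assumes that any one significant outcome would be taken as support, which the article neither states nor excludes.

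Second, the significance condition on partial eta-squared affects the mixed models only, but these include every primary-aim outcome. For a 1-df interaction at n = 20 the cut-off lies between about 0.066 and 0.187, depending on error df. A true 0.12 would average about 0.16 to 0.30 among the values calculated.

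The matter should be corrected before analysis. It does not invalidate the design.

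**What to change.** Keep the time-by-condition interaction as the tested contrast, since the sample size rests on it. Then do one of two things:

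- name one of LT, LAcc, MVAS and RPE as primary and test it at 0.05; or
- apply Holm across the four and state that the adjusted results decide the first hypothesis.

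Which outcome to name is the investigators' choice, because nothing in the article ranks them. State that RT, RAcc and the ratings taken only at T2 are exploratory, as the Aims already imply. Replace the effect-size sentence for the mixed models with one saying that the estimate, 95% CI and standardised effect size are reported for every mixed-model outcome regardless of p.

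**Cost.** The text is a short paragraph. A single primary outcome leaves the planned minimum of 15 unchanged. Holm costs some power, at most that of Bonferroni at 0.05/4 = 0.0125. In the m = 4 set-up that reproduces the plan's own figure, Bonferroni needs N = 19 for 90% power. Power is 0.92 at N = 20, 0.85 at 17 and 0.78 at 15, so the planned 20 can absorb it only if dropout is small. These figures depend on that set-up: with m = 2 in the same formula, power at N = 20 falls from 0.88 at alpha 0.05 to 0.70 at 0.0125. Reporting all effect sizes costs nothing.

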## Introduction

1

Fencing is an open-skilled combat sport characterized by high intermittency [1], with short bursts of sword fighting and frequent rest intervals [2]. This leads to non-maximal physiological demands and relatively minor physical fatigue [3]. Fencing, however, requires the allocation of mental resources and perceptual-cognitive skills (e.g., sustained attention, information processing, response inhibition) for performance maintenance and success [[4], [5], [6]]. The prolonged interaction between motor and cognitive demands in the congested competition format (i.e., featuring consecutive preliminary and elimination bouts on the same day) can cause the onset of mental fatigue in fencers [7,8]. Longitudinal tracking during a national championship revealed elevated perceived mental fatigue and slower reaction time (RT) after competitions, suggesting a detrimental effect of mental fatigue on fencing performance [8]. During the period, the daily baseline mental fatigue fluctuated and peaked on competition days [8]. Furthermore, in the early stage of the consecutive bout progression, mental fatigue tended to accumulate faster [8]. This highlights the importance of mental fatigue management since the competition mornings [9]. The pre-competition preparation period, which may first determine the initial state of mental fatigue and subsequent competitive performance, emerges as a valuable time window worthy of attention.

Pre-competition warm-up is vital to attain optimal performance by evoking temperature, metabolic, neural, and psychological-related effects [10]. Meanwhile, warm-up strategies across sports are developed largely through a trial-and-error basis and the coach's experience [10]. Typically, a pre-competition warm-up protocol in fencing includes a generalized physical section, and the coach or sparring partner-led, technical/tactical drills and combat in a specialized section that requires a 1:1 personnel configuration to meet its high-level, competition-like demands. Yet, scientific evidence is lacking regarding the effect of such a warm-up on subsequent fencing performance. Moreover, mental fatigue could arguably build up due to the specific motor-cognitive demands from the warm-up combat, exacerbating its accumulation throughout the forthcoming competition day [9]. Further optimization of the warm-up could potentially enhance the performance [11,12] but lower the risk of prematurely elevating mental fatigue in fencers.

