### Study design

2.1

The study will employ a within-subjects, randomized crossover design. Participants will be paired (i.e., matched pairs) by the head coach according to registered gender and athletic level. After the familiarization, each matched pair will be randomly assigned in a counterbalanced manner to either commence with the experimental condition (EXP) or the control condition (CON) first. A pre- (T0) and post-test battery (T2) will be conducted for the two conditions (see Fig. 1). Additionally, immediately before VR combat (VC) and traditional one-on-one combat (TC) in the specialized warm-up, the subjective perceptions will be checked again (T1) for standardization.

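### The mixed models leave out visit order and visit-within-fencer variance, so the interaction test loses power and between-condition contrasts become too liberal if a fencer's state differs between days

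*Protocol article*

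**What the plan says.** The Study design section describes a crossover ("The study will employ a within-subjects, randomized crossover design") in which "each matched pair will be randomly assigned in a counterbalanced manner to either commence with the experimental condition (EXP) or the control condition (CON) first". Under Procedures, the two conditions are run on different days ("The washout period will be at least 48h between conditions"), after a familiarization visit. Measurements sit inside visits: "A pre- (T0) and post-test battery (T2) will be conducted for the two conditions", and the questionnaire is also given at T1.

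For RT, RAcc, LT, LAcc, MVAS and RPE, the Statistical analyses section specifies a linear mixed model with "fixed-effect factors for time, condition, and their interaction, and a random intercept for ID". VAS-Re, VAS-Enj, NASA-TLX and HRmean, with one value per condition, are compared by paired t-test. Missing data are deleted by case. No visit, period or sequence term and no visit-level random effect is named anywhere. The Participants section bases the sample size on the time x condition interaction.

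**The concern.** With a fencer intercept as the only random effect, T0 and T2 on one day are treated as no more alike than readings from two different days. Sleep, workload or mood on the day can move both readings of a visit together, and the Introduction reports that in earlier monitoring "the daily baseline mental fatigue fluctuated and peaked on competition days". If that happens here, the model uses one residual for comparisons that need two different error terms: within-visit change (time, time x condition) and between-visit difference (condition, and EXP versus CON at T2).

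Separately, PVT-B and FST are taken at both visits, so a shift from the first to the second is plausible. Counterbalancing keeps it from biasing the comparison while the two orders stay equal in size, but an unmodelled shift still goes into the error. At stake are the power of the test that sizes the trial and the false-positive rate of claims about condition.

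**Working it through.** **Inputs from the protocol article.** 20 fencers (10 pairs, so 10 fencers per order if balanced); 2 conditions on 2 days; 2 time points for RT, RAcc, LT and LAcc, 3 for MVAS and RPE; partial eta squared 0.12, alpha 0.05, power 0.90, correlation 0.5, epsilon 1, minimum N 15.

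**Assumptions, not in the documents.** Within-visit error variance se² = 1; visit-within-fencer variance sv² = 0.25, 0.5 or 1; visit shift p = 0, 0.5 or 1 error SD.

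**1. The stated sample size.** f² = 0.12/0.88 = 0.136, so f = 0.369. For four repeated readings, lambda = f² x N x 4/(1 − 0.5). At N = 15, lambda = 16.4 on 3 and 42 df and power is 0.915; at N = 14 it is 0.892. The figure of 15 reproduces. One common correlation among all four readings carries the same assumption as the planned model: no extra similarity within a day.

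**2. Error terms with two time points.** The planned residual has 79 − 19 − 3 = 57 df. Its expectation, against the error that each test needs, is:

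| sv²/se² | planned residual, 1 + (2/3)sv² | needed for time and interaction, 1 | needed for condition, 1 + 2sv² | needed for T2 contrast, 1 + sv² |
|---|---|---|---|---|
| 0.25 | 1.17 | 1 | 1.50 | 1.25 |
| 0.5 | 1.33 | 1 | 2.00 | 1.50 |
| 1 | 1.67 | 1 | 3.00 | 2.00 |

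The residual is too large for the interaction and too small for the other two.

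**3. Simulated consequences** (20 fencers, 10 per order, no visit shift). Power is for a true interaction of 1.49 error SD, chosen to give 90% in the correct model.

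| sv²/se² | interaction type I | interaction power | condition type I | T2 contrast type I |
|---|---|---|---|---|
| 0 | 5% | 90% | 5% | 5% |
| 0.25 | 3.4% | 88% | 8.5% | 6% |
| 0.5 | 2.4% | 84% | 11% | 6.5% |
| 1 | 1.3% | 77% | 14% | 7% |

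With three time points and sv²/se² = 1, the condition type I error is about 22%. With a visit effect and a visit-within-fencer stratum in the analysis, type I error returns to about 5% for interaction and condition in every scenario, and interaction power stays at 90%.

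**4. Visit shift, balanced orders, sv² = 0.** Each of the 80 readings moves by p/2 either way, which adds 80 x (p/2)²/57 = 0.35p² to the residual. The shift cancels from the interaction estimate if it is equal at T0 and T2. For p = 0.5 and 1, interaction type I error is 4.0% and 2.4%, and power 89% and 84%. With p = 1 and sv² = 1 together, power is 68%.

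**5. Visit shift, unequal orders.** EXP minus CON carries −p in fencers who start with EXP and +p in the others. The net bias has size p x (nA − nB)/(nA + nB). At 10 versus 6 fencers it is p x 4/16 = 25% of the shift, in the condition and T2 contrasts.

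**6. Paired t-tests.** With one value per visit, the difference already contains the visit variance, so the error term is right. Under balance, a shift of 0.5 or 1 SD makes these tests conservative (type I error 1.7% to 4.4%).

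**The case against.** The strongest reply is that the design already limits the problem. Order is randomised and counterbalanced. Familiarization covers the whole test battery, with repeats where needed. Sessions use a fixed slot, each visit has its own T0, and the eligibility criteria rule out competitions during the study and classes, examinations or recent caffeine before tests. The fluctuation cited in the Introduction was seen around a championship, so it does not show a large visit variance in these training sessions. All this stands as a reason to expect a smaller effect, and it is why the range starts at 0.25, where the power loss is only about two points. It does not put the missing terms in the model, and familiarization does nothing about day-to-day variation.

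The 90% starting power is a reference point, not the protocol's: its own inputs give about 98% at N = 20. The 25% bias needs all four lost fencers to come from one order.

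A reader might also infer more than the documents support:

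- That every planned test is distorted. The paired t-tests are not affected by visit variance.
- That the interaction test will produce false positives. It becomes conservative.
- That the VR game is practised from one condition visit to the next. After familiarization it is played only in EXP.
- That the planned sphericity test is empty. It has nothing to test for the outcomes with two time points, but MVAS and RPE have three. In neither case does it supply the missing variance term.

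A separate analysis plan would not settle the matter, because the article states both the fixed and the random effects of this model.

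**Conclusion.** The point holds for the mixed models. As written, they do not match readings nested in two separate-day visits. For any non-zero visit variance the direction is certain: the interaction and time tests lose power, the condition main effect becomes too liberal, and the T2 contrast mildly so. The size is not known from the documents. The figures rest on an assumed variance ratio of 0.25 to 1, two time points, 20 fencers in balanced order and an assumed 90% starting power. An unmodelled visit shift adds to the loss of power, and it biases the condition and T2 contrasts only if dropout leaves the orders unequal. Confidence is high in the omission and moderate in its size. It should be corrected before analysis, but it does not invalidate the design.

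**What to change.** In each mixed model, add visit number (1 or 2) and visit x time as fixed effects and a random intercept for visit within ID, beside the intercept for ID. Name a small-sample df method such as Satterthwaite. Analyse VAS-Re, VAS-Enj, NASA-TLX and HRmean with condition and visit number as fixed effects and ID as random, in place of the plain paired t-test.

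The cost is a change of model formula, since visit order is known for every fencer, and fewer error df. With two time points and 20 fencers, the visit stratum has 20 − 2 = 18 df for condition and the within-visit stratum 40 − 3 = 37 for the interaction, against 57 in the pooled residual. In the simulations, interaction power still held at 90% with a separate within-visit error term on 38 df.
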